### NMR Measurements

Thawed 400 μL urine samples will be mixed with 200 μL of a 0.75 M phosphate buffer solution (containing 0.5 % sodium trimethylsilylpropionate-d4 (TSP)) prepared in D_2_O and transferred to a 5 mm NMR tube. Thawed 200 μL blood serum samples will be mixed with 400 μL D_2_O and transferred to a 5 mm NMR tube. All ^1^H NMR spectra will be collected on a Varian 500 MHz NMR spectrometer (Agilent technologies, Santa Clara, United States) equipped with a 5 mm PFG One NMR probe. One dimensional(1D) NOESY-Presaturation pulse sequence for urine and 1D Carr-Purcell Meiboom-Gill (cpmg) experiment for blood serum will be used. Each free induction decay (FID) will be collected using a total of 128 scans with a relaxation delay of 2 s.

### Multivariate data analysis for metabolomics study

All ^1^H NMR spectra will be manually phased, baseline-corrected and reference to TSP (0.0 ppm) using ACD software (ACD/Labs, Ontario, Canada). Region containing water (4.5–5.2 ppm) and TSP (0.0–0.2 ppm) will be excluded. Each ^1^H NMR spectra will be segmented in bins of 0.04 ppm. Urine spectra will be normalized based on creatinine peak and serum spectra will be normalized based on the glucose peak area. All binned data will be imported into SIMCA (Version 14.0, Umetrics, Umea, Sweden). The binned data will be pareto-scaled prior to multivariate statistical analysis. Multivariate data analysis including unsupervised principal component analysis (PCA), and supervised partial least square discriminant analysis (PLS-DA) will be performed. PCA will be used to obtain a general overview of the metabolites and to detect outliers. PLS-DA will be performed to separate different groups. The quality of the model will be described by the parameter of R^2^ and Q^2^ which represent model fitness and predictive ability. All PLS-DA models will be validated using the permutation test. An overall *p*-value of 0.05 based on the Bonferroni correction will be used.

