The objective of this trial is to investigate the effectiveness and safety of *C. caudatus* in patients with type 2 diabetes by addressing the following hypothesis (1) *C. caudatus* supplementation will improve the glycemic status in patients with type 2 diabetes (2) *C. caudatus* supplementation will improve inflammation marker, oxidative stress marker and lipid profile in patients with type 2 diabetes (3) *C. caudatus* supplementation is safe and will not result in adverse effects (4) the therapeutic effect of *C. caudatus* will result in changes in urine and serum metabolome.

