#### Secondary outcomes

Secondary outcomes in this study include changes in other glycemic parameters such as fasting glucose, insulin, fructosamine, changes in lipid profile (triglyceride, total cholesterol, HDL-cholesterol, LDL-cholesterol), changes in inflammation (high-sensitivity C-reactive protein) and oxidative stress marker (plasma malondialdehyde), changes in anthropometry parameters (BMI, waist circumference), changes in metabolite profile (urine, serum), changes in safety parameters (liver profile and renal profile), changes in blood pressure, dietary pattern and physical activity.

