### Procedure

After obtaining the informed consent, both groups will be required to attend clinical research center on 4 occasions- baseline, week 4, week 8 (end of study) and week 12 (post study follow-up). Subjects will be interviewed regarding their socio-demographic background at baseline. At each follow-up, all subjects will undergo a physical examination which include anthropometric, blood pressure, blood test, urine test and completed a dietary history questionnaire and international physical activity questionnaire (IPAQ).

Anthropometry measurements including weight, height and waist circumference will be measured. Body height will be measured using SECA stadiometer model 217 (SECA, Hamburg, Germany) to the nearest 0.1 cm. Body weight will be measured using a SECA electronic scale model 703 to the nearest 0.1 kg (SECA, Hamburg, Germany). Waist circumference in cm will be assessed midway between the lowest rib and the iliac crest using a non-stretchable tape measure. BMI will be calculated using World Health Organization classification [30]. Blood pressure will be measured using an automatic blood pressure monitor (Omron, Kyoto, Japan).

Blood sample will be drawn after an overnight fasting from the antecubital vein with patients in seated position. The volume of blood taken will be 10 ml, collected in four different pre-chilled tubes. A plain evacuated blood collecting tube will be used to collect 4 ml blood for metabolomic analysis. One milliliter will be taken in potassium oxalate/sodium fluoride tubes for fasting glucose. Another 1 ml blood sample will be taken in tubes containing ethylenediaminetetraacetic acid (EDTA) for HbA1C. The remainder 4 ml blood will be collected in the heparinized tube for other biochemistry parameters. Blood will be drawn by trained nurses and immediately placed on ice in the dim light environment. Blood sample that are collected will be centrifuged at 3000 rpm for 10 min at 4 °C to obtain the serum and plasma. 15 ml urine samples will be collected in the polyethylene containers. Blood and urine sample that are collected will be stored at −80 °C until further analysis.

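### Serum NMR spectra are normalised to glucose, which the treatment is expected to lower; a glucose effect would be misattributed to the other serum metabolites

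*Protocol article*

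**What the plan says.** The section on multivariate data analysis fixes one normaliser per fluid. For urine: "Urine spectra will be normalized based on creatinine peak". For serum: "serum spectra will be normalized based on the glucose peak area". The binned, normalised data are then pareto-scaled and passed to PCA and PLS-DA. The PLS-DA models are to be checked by permutation, and a Bonferroni correction is to hold the overall p-value at 0.05.

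The end of the Background lists four hypotheses. The first is that "supplementation will improve the glycemic status in patients with type 2 diabetes". The fourth is that the therapeutic effect "will result in changes in urine and serum metabolome". Under Secondary outcomes the trial will assess "changes in other glycemic parameters such as fasting glucose, insulin, fructosamine", and the same list includes the urine and serum metabolite profile. The Background also cites a rat study with a significant fall in fasting glucose as part of the rationale. The Discussion counts glucose among the most prominent signals in serum spectra.

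The article gives no reason for choosing glucose, and plans no second normalisation of serum and no adjustment for measured glucose.

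**The concern.** Normalisation should remove differences between spectra that have nothing to do with the question, such as dilution or instrument gain. The reference must therefore be something that treatment leaves alone. Here it is the analyte that the trial most expects to move.

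Dividing by it does two things when the treatment works. It fixes the NMR glucose signal at a constant, so the change most relevant to the hypothesis disappears from the serum profile. It also spreads the inverse of that change over all the other signals. A reader of the PLS-DA loadings could then report changes in amino acids, lactate or lipids that come from the denominator. The Discussion already links raised branched-chain amino acids to insulin resistance, so an artificial rise could readily be given a biological reading.

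**Working it through.** The document states no figure on this point, so there is none to reproduce. The check is algebra on a ratio.

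**Inputs.** From the document: the normaliser is glucose peak area, and treatment is expected to improve glycemia. Assumed, because the document gives no value: the relative fall g in glucose, taken from 5% to 30%.

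**Step 1: one metabolite, one arm.** After normalisation each signal is M/G, where M is the metabolite signal and G the glucose signal. Let treatment change G to G(1−g) and leave M alone.

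- Normalised metabolite: M / [G(1−g)] = (M/G) × 1/(1−g)
- Normalised glucose: G(1−g) / [G(1−g)] = 1, as before treatment

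| Fall in glucose, g | Apparent change in an unaffected metabolite, 1/(1−g) − 1 | Apparent change in normalised glucose |
|---|---|---|
| 5% | 1/0.95 − 1 = +5.3% | 0% |
| 10% | 1/0.90 − 1 = +11.1% | 0% |
| 15% | 1/0.85 − 1 = +17.6% | 0% |
| 20% | 1/0.80 − 1 = +25.0% | 0% |
| 30% | 1/0.70 − 1 = +42.9% | 0% |

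**Step 2: metabolites that do change.** The factor is common to all of them, so it need not show as a rise. With g = 10%, a metabolite that truly falls by 5% appears at 0.95/0.90 = 1.056, a rise of 5.6%. One that truly falls by 10% appears unchanged. One that truly falls by 15% appears at 0.85/0.90 = 0.944, a fall of only 5.6%.

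**Step 3: two arms.** Both arms receive lifestyle advice, so glucose may also fall in controls. With falls g_U (treated) and g_C (control), the distortion between arms is (1−g_C)/(1−g_U). It vanishes if the falls are equal. In that case each arm still shows the Step 1 factor when visits are compared. The between-arm error is therefore present when the treatment has the glycemic effect that it is being tested for.

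**Step 4: do the planned safeguards catch it?**

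- Pareto scaling rescales each bin across all spectra and leaves the relative difference between arms in place.
- A permutation test asks whether the separation could arise by chance. The arms really do differ on M/G, so a model built on that difference can pass.
- A Bonferroni correction moves the significance threshold. It does not move the shifted mean.

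**The case against.** **Scope.** The strongest reply is that little of the trial depends on this. That stands. HbA1C, the primary outcome, is a separate assay, as are fructosamine, insulin and the lipids. A reader might infer that a real glucose effect would be lost from the trial. It would not: Biochemical assessments specifies a hexokinase assay for fasting glucose, and that result is compared between arms as usual. Only the NMR glucose signal is lost.

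**Hypothesis (4) itself.** If glucose alone fell, the serum metabolome did change, so a finding of some change would be true. The error lies in which metabolites get the credit.

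**Error rates.** A reader might want a false-positive rate. With assumed log-SDs of 0.25 (metabolite) and 0.30 (glucose), treated as independent, an unadjusted two-sample t-test at 5% would flag an unaffected metabolite in about 20% to 27% of trials for a 10% fall, and 65% to 81% for a 20% fall. The two ends of each range are 35 per arm (50 less 30% drop-out) and 50 per arm. But the plan uses PLS-DA with a Bonferroni correction. If that covers 20 to 200 tests, itself an assumption, the same rates become about 0.5% to 4% and 8% to 41%. The SDs are not in the document either. Such rates only illustrate; the factor 1/(1−g) does not depend on them.

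**Variation in glucose swamping every bin.** This too might be inferred, and it is not shown. With the SDs above, glucose contributes 0.09/(0.09 + 0.0625) = 59% of the log-variance of the ratio. For a metabolite with log-SD 0.5 it contributes 0.09/(0.09 + 0.25) = 26%.

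**Sample handling.** The Procedure section says "A plain evacuated blood collecting tube will be used to collect 4 ml blood for metabolomic analysis", while fasting glucose has its own fluoride tube, so one might suspect that glucose decays in the metabolomics sample. The same section calls for pre-chilled tubes, immediate placing on ice and centrifugation at 4 °C, and laboratory staff are blinded to allocation. The documents do not support a handling bias.

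**Chemical-shift reference.** NMR Measurements mentions TSP only in the urine buffer; 200 μL "blood serum samples will be mixed with 400" μL of D2O. The analysis section references all spectra to TSP. A reader might conclude that the serum step is impossible. The article may simply omit a reagent, so this is a minor inconsistency, separate from the normaliser.

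**Conclusion.** The point holds for the serum metabolomics analysis. The plan fixes a normaliser that its own first hypothesis expects to change, and nothing in the document compensates. The size is a common factor of 1/(1−g) on every serum signal other than glucose, or +5.3% to +25% for an assumed relative fall of 5% to 20%, with no visible change in NMR glucose. The factor follows from the stated rule; only g is assumed. Between arms, g is the fall relative to control.

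The consequence is misattribution in one part of one secondary outcome and in the serum half of hypothesis (4). The primary analysis, the laboratory glucose result and the urine spectra are not affected. If glucose does not differ between arms or visits, no systematic shift arises, and the shared denominator only adds common noise to the bins.

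**What to change.** Replace glucose-peak normalisation of serum with a method that does not hang on a single treatment-affected metabolite. Two suitable options are probabilistic quotient normalisation, or a fixed sample volume with a reference standard. Keep glucose as an analysed signal, so that its NMR change can be seen beside the hexokinase result.

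Total spectral area without the glucose and water regions is better kept as a sensitivity analysis. Hypothesis (2) expects the lipid profile to change, and the Discussion lists lipoprotein fat among the prominent serum signals, so that total may also move with treatment.

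Separately, and minor: reconcile the TSP statements in NMR Measurements and in the multivariate analysis section, and state what serum spectra are referenced to.

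The cost is small. Probabilistic quotient normalisation is a processing step that needs no new samples or visits. A reference standard would have to be arranged when the spectra are acquired. The urine normalisation needs no change on this account.

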## Abstract

**Background:**

Type 2 diabetes mellitus is a major health threat worldwide. *Cosmos caudatus* is one of the medicinal plants used to treat type 2 diabetes. Therefore, this study aims to determine the effectiveness and safety of *C. caudatus* in patients with type 2 diabetes. Metabolomic approach will be carried out to compare the metabolite profiles between *C. Caudatus* treated diabetic patients and diabetic controls.

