Medicinal plants have been used as traditional medicine for treating diseases, and their uses are considered safer than the oral anti-diabetic drugs [14]. The discovery of metformin, from the *Galega officinalis* has augmented the interest to quest for more natural products to treat diabetes [15]. *Cosmos caudatus*, or known locally as *Ulam Raja*, is a medicinal herb found in tropical countries [16]. It has been identified as one of the ten commonly used medicinal plants in Malaysia for treatment of type 2 diabetes [17]. *C. caudatus* contained a variety of bioactive compounds, such as ascorbic acid, quercetin, proanthocyanidin, chlorogenic acid and catechin [18–21]. *C. caudatus* has been reported to have an extremely high antioxidant capacity of about 2500 mg ascorbic acid equivalent antioxidant capacity (AEAC) per 100 g of fresh samples as compared to orange and guava which had 142 mg and 270 mg AEAC, respectively [22]. Its high antioxidant content may suggest its potential in reducing the oxidative stress [20].

In addition, *C. caudatus* have been shown to possess various medicinal benefits [16] including anti-diabetic [23], antihypertensive [24] and anti-inflammatory effect [25] in animal studies. Recent pre-clinical study in rats indicated a significantly reduction in fasting blood glucose, and a significant improvement in lipid profile after 4 weeks of supplementation [23]. Preliminary study in healthy volunteers has shown that there was a steady reduction in the postprandial blood glucose after consuming rice and fresh *C. caudatus* (unpublished data). However, the effect of *C. caudatus* in patients with type 2 diabetes remains unclear.

Metabolomics is an unbiased approach to measure metabolites disturbance within a biological system at a given time [26]. The profiling of these metabolite can provide detailed information on the metabolic pathways [27]. Additionally, metabolites levels are influenced by environmental factors such as diet and lifestyle factors [28]. Therefore, by using metabolomics approach, it provides a clearer understanding of the effect of *C. caudatus* in patients with type 2 diabetes.

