### Intervention

#### Diabetic *C. caudatus* treated (U) group

The *C. caudatus* seeds were obtained from the Institute of Bioscience, Universiti Putra Malaysia (UPM) and planted at the Universiti Putra Malaysia Agricultural Park. A voucher specimen (No. SK 2400/14) has been deposited in the herbarium, Biodiversity Unit, Institute of Bioscience, Universiti Putra Malaysia. Fresh *C. caudatus* will be provided to the *C. caudatus* treated (U) group twice a week for 8 weeks. The *C. caudatus* will be vacuum packed in a zip-lock bag before distribution. Patients in *C. caudatus* treated (U) group will be asked to consume raw *C. caudatus* leaves (15 g) daily together with one of the main meal (either lunch or dinner) for 8 weeks.

*C. caudatus* supplementation will be given simultaneously with the usual diabetes care that includes maintenance of the oral anti-diabetic drugs dosage and compliance with the dietary and physical activity recommendations. In addition, patients in *C. caudatus* treated (U) group will be advised to perform self-monitoring blood glucose. Glucometer and strips will be given to the patients to record three values daily (after fasting, before a meal and two hours after a meal). All the patients will be educated on how to use the glucometer.

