#### Diabetic control (C) group

The diabetic control (C) group will be asked to abstain from consuming *C. caudatus* for 8 weeks . Both groups will be given standard lifestyle interventions which include medical nutrition therapy and physical activity enforcement). In addition, both groups will be educated for the concepts of carbohydrate exchange and serving sizes. Patients in diabetic control (C) group will be encouraged to eat the same serving of fruits and vegetable as the *C. caudatus* treated (U) group. Likewise, patients in diabetic control (C) group will be advised to perform self-monitoring blood glucose. Glucometer and strips will be given to both groups to record three values daily (after fasting, before a meal and two hours after a meal). All the patients will be educated on how to use the glucometer.

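### Hypothesis 4 speaks of a therapeutic effect on the metabolome, but a PLS-DA of leaf eaters against abstainers can show only that supplementation changes the spectra

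*Protocol article*

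**What the plan says.** All references are to the protocol article.

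- **Hypothesis (Background, objectives).** The fourth hypothesis is that "the therapeutic effect of *C. caudatus* will result in changes in urine and serum metabolome". The Discussion adds that the results will inform the mechanism of a therapeutic effect.
- **Contrast (Abstract, Background).** The metabolomic aim is to "compare the metabolite profiles between *C. Caudatus* treated diabetic patients and diabetic controls".
- **Exposure.** Treated patients eat raw "leaves (15 g) daily together with one of the main meal (either lunch or dinner) for 8 weeks". In the other arm, "The diabetic control (C) group will be asked to abstain from consuming" the plant over the same 8 weeks. Controls are also encouraged to match the treated arm's fruit and vegetable servings.
- **Leaf content (Background).** The leaf contains bioactive compounds "such as ascorbic acid, quercetin, proanthocyanidin, chlorogenic acid and catechin". The same section says that metabolite levels respond to diet and lifestyle.
- **Analysis (Multivariate data analysis for metabolomics study).** Only the water and TSP regions are removed. The rest is cut into 0.04 ppm bins, normalized and Pareto-scaled. After PCA, "PLS-DA will be performed to separate different groups". Model quality is described by R2 and Q2, models are validated by permutation, and an overall 0.05 level with Bonferroni correction applies.
- **Softer wording (Discussion).** Later the Discussion describes the aim as studying metabolic disturbance due to supplementation, without calling it therapeutic.

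**The concern.** The hypothesis is about why the metabolome changes; the analysis addresses only whether it differs between arms. In weeks 4 and 8, eating the leaf is tied to the group label by design. Any compound that comes from the leaf and reaches the spectrum is a marker of allocation, whether or not glucose metabolism has moved. A classifier trained on allocation will use such markers if they are there.

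At stake is the interpretation of one secondary outcome and one of four hypotheses. A well-validated separation could be described as evidence of mechanism when it is partly or wholly a record of what patients ate.

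**Working it through.** No figure in the article can be reproduced on this point, so the check is a comparison of claim and test, followed by an illustration.

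**1. What the test can reject.** For bin *j*, write the mean difference between arms as Δj = Ij + Tj. Ij is signal from the eaten leaf and Tj is change in the patient's own metabolism through an effect on diabetes. The permutation test assumes that group labels are exchangeable, that is, Δj = 0 for all bins. Hypothesis 4 concerns Tj. Labels stop being exchangeable if any Ij is non-zero, even with every Tj = 0. R2 and Q2 measure how well the spectrum fits and predicts the label, and the Bonferroni step controls how often a chance Δj is declared real. None of them splits Δj into its parts.

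**2. Whether a few bins are enough.** The inputs were:

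- Bins: excluding 0.0–0.2 ppm and 4.5–5.2 ppm, with an assumed upper limit of 10 ppm, (10 − 0.2 − 0.7)/0.04 = 9.1/0.04 = 227.5, taken as 227.
- Patients: 50 per arm (Sample size), and 50 × (1 − 0.30) = 35 per arm after the stated drop-out rate.
- Therapeutic effect: Tj = 0 in every bin.
- Leaf signal (assumed): 0, 5 or 10 bins raised in the treated arm by 1 or 2 SD.
- Model: two-component PLS-DA, Pareto scaling, Q2 = 1 − PRESS/SS by seven-fold cross-validation.
- Test: p = (1 + number of permuted Q2 values at or above the observed)/(59 + 1), with 60 simulated trials per row.

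| Leaf bins, shift | 50 per arm: p ≤ 0.05 | mean Q2 | 35 per arm: p ≤ 0.05 | mean Q2 |
|---|---|---|---|---|
| none | 2% | −0.41 | 5% | −0.46 |
| 5, 1 SD | 73% | 0.00 | 62% | −0.05 |
| 5, 2 SD | 100% | 0.57 | 100% | 0.48 |
| 10, 1 SD | 100% | 0.34 | 97% | 0.19 |
| 10, 2 SD | 100% | 0.80 | 100% | 0.74 |

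With 60 trials the simulation error is about 6 percentage points at 73% (√(0.733 × 0.267/60) = 0.057).

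In the weakest non-null case, 5 bins at 1 SD, the permutation test usually passes but mean Q2 is about zero, so a reader who also weighs Q2 would not be impressed. In the other cases both criteria look favourable with no therapeutic effect at all. The simulation shows what follows if leaf signals of this size exist; it does not show that they do.

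**The case against.** The strongest reply has four parts.

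**The documents do not show leaf signals in the spectra.** They list compounds in the leaf but say nothing of their excretion or breakdown products. They also say that NMR is less sensitive than mass spectrometry, and the prominent serum and urine signals they name are not presented as leaf markers. Blood is drawn after an overnight fast. This stands: detectability is an assumption, and the concern is greater for urine, for which no fasting or timing rule is given, than for fasting serum.

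**Controls match fruit and vegetable servings.** This stands in part. It should narrow differences in plant compounds common to many foods, but it supplies neither this leaf nor its particular mix.

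**Peaks can be identified afterwards, and interpretation of loadings may sit in a fuller plan.** Fair: the article notes that a good spectral library exists, and the lack of a leaf-signal filter in a condensed article is no fault by itself. What remains is that the stated hypothesis goes further than the stated test.

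**No rule says that a passing model will be called therapeutic.** A reader might infer that the trial would report a therapeutic mechanism on a significant permutation test even with flat HbA1C. The documents contain no such rule. HbA1C and the other glycemic measures are assessed separately, and the Discussion's wording about disturbance due to supplementation is within the design's reach.

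A reader might also try to size the problem from the article's antioxidant figures: 15 g at 2500 mg AEAC per 100 g is 375 mg a day. That is antioxidant capacity, not the amount of any compound or the height of any NMR peak, so it does not measure the problem.

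**Conclusion.** The point holds as a mismatch between claim and test, and as a cheap improvement. The randomized comparison can support a statement that supplementation changes the urine or serum metabolome. It cannot, by R2, Q2 and permutation alone, support the statement that a therapeutic effect did so.

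It would be too strong to say that the leaf will separate the arms or that the metabolomic comparison is invalid. The conclusion is that leaf signals could separate them. This rests on the design, on the article's own statement about diet, and on the assumption that some leaf-derived signals are visible by NMR. Under the shifts assumed above, 5 to 10 of 227 bins gave permutation p ≤ 0.05 in 62% to 100% of null-effect trials.

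The consequence is confined to the metabolite profile, a secondary outcome; the primary HbA1C conclusion is unaffected.

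**What to change.** 1. **Reword hypothesis 4** as an effect of *C. caudatus* supplementation on the urine and serum metabolome, in line with the Discussion's softer wording, and temper the Discussion's mechanism claim to match.
2. **Flag bins before modelling.** List those attributable to the leaf or to known dietary breakdown products, from library assignments and, if wanted, one leaf-extract spectrum. An extract alone will not show products formed in the body, so the library step is needed. Fit the week 4 and week 8 PLS-DA with and without the flagged bins, and describe separation that depends on them as a marker of intake.
3. **Limit mechanistic claims** to remaining endogenous metabolites whose change relates to change in HbA1C, fasting glucose or fructosamine. Separation that survives bin removal does not by itself prove a therapeutic effect. For serum, the planned normalization to the glucose peak ties every other bin to glucose by construction, so this association must be read with that in mind.
4. **Use week 12 descriptively only.** A real but reversible effect would also fade once the leaf stops, and control abstention is specified for 8 weeks only.

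The cost is a text change, a second model fit on data already collected and at most one extra NMR run. A few bins of mixed dietary and endogenous origin would leave the mechanistic model. No extra patients or visits are needed.
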